**Methods/design:**

This is a single-blind randomized controlled trial with a nested qualitative study. Seventy-five severe MS-carer dyads are being randomized (at three centers, one in each area of Italy) to HPA or usual care (UC) in a 2:1 ratio. Each center has a specially trained team consisting of four professionals (physician, nurse, psychologist, social worker). The team makes a comprehensive assessment of the needs of the dyads. HPA content is then agreed on, discussed with the patient’s caring physician, and delivered over six months. The intervention is not intended to replace existing services. At later visits, the team checks the HPA delivery and reviews/modifies it as necessary.

HPA and UC dyads are assessed at home by a blind examiner at baseline, and three and six months later; they also receive monthly telephone interviews. Dyads assigned to UC receive the examiner’s visits and telephone interviews, but not the team visits.

Primary outcome measures are changes in symptoms (Palliative care Outcome Scale-Symptoms-MS, POS-S-MS), and quality of life (the Schedule for the Evaluation of Individual Quality of Life-Direct Weighting (SEIQoL-DW), not assessed in patients with severe cognitive compromise) at three and six months. Other outcomes are changes in patient functional status and mood; changes in carer quality of life, mood and caregiving burden; costs; incorporation with standard care; unplanned hospital admissions; referrals to hospice; and deaths.

The experience of participants will be evaluated qualitatively by individual semi-structured interviews (HPA patients and carers) and focus group meetings (HPA patients’ caring physicians).

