#### Primary outcomes

Primary outcomes are changes in patient HRQOL (Schedule for the Evaluation of Individual Quality of Life-Direct Weighting, SEIQoL-DW) and MS symptoms (Palliative care Outcome Scale-Symptoms-MS, POS-S-MS). The SEIQoL-DW is a brief instrument, derived from the schedule for evaluation of individual quality of life (SEIQoL). It allows respondents to nominate areas of life that are most important in determining their HRQOL. The level of satisfaction/functioning in each of these areas is then recorded [22-26]. The SEIQoL-DW index is obtained from the satisfaction with and weighting for each area, and ranges from 0 (worst possible score) to 100 (best possible score). SEIQoL-DW has been used in neurological diseases [27-30], and was the primary outcome measure of the Ne-Pal trial [15].

POS-S-MS (primary outcome measure) and the Core-Palliative care Outcome Scale (Core-POS) were developed and validated for use with palliative care patients to assess emotional, psychological and spiritual needs, and provision of information and support [31,32]. Core-POS has been used in patients with advanced cancer and other conditions including dementia, motor neuron disease, and MS [33,34]. It consists of 10 items, which are scored from 0 (best) to 4 (worst). The score is the sum of the scores from each question, and therefore can range from 0 to 40. There are patient, carer, and staff versions, each requiring about 10 minutes to complete [31,35]. Generally, the patient is asked about needs over the preceding three days, but other time frames have been used [36]: in this study, we asked about the preceding seven days.

POS-symptoms (POS-S) is a scale enquiring about 10 symptoms with two open questions (which symptom affected the patient the most; which improved most). It was developed for use in cancer patients and is used alongside the Core-POS for assessing common physical symptoms. Disease-specific versions of POS-S have been developed for end-stage kidney disease, Parkinson’s disease, and MS [33]. POS-S-MS comprises 18 items relating to MS symptoms, plus an open question (0 to 4 scale) over the preceding seven days [34].

The psychometric properties of Core-POS and POS-S-MS have been assessed in patients with severe MS: both are acceptable, reliable, and valid in this population [34].

In the present RCT, MS patients with severe cognitive impairment do not complete the questionnaires: the caregiver versions of Core-POS and POS-S-MS are used.

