#### Sample size

The sample size was based on previous data for SEIQoL-DW [15] and POS-S-MS [8]; for both outcomes we considered changes at three months compared to baseline.

SEIQoL-DW: a sample size of 21 patients assigned to HPA (study intervention) and 11 assigned to UC (control) has a power of 80% to detect an assumed mean change of score of 31.5 (standard deviation (SD) 12.8) in the HPA group compared to a change of 12.1 (SD 19.3) (null hypothesis) in the UC group, at alpha level 0.05 using a two-sided, two-sample *t* test. Assuming 20% dropout, 25 patients are required in the HPA group and 13 in the UC group (total sample size 38).

POS-S-MS: a sample size of 41 HPA and 21 UC has a power of 85% to detect an assumed mean change of −0.4 (SD 0.5) in the HPA group, with a concomitant change of 0.2 (SD 0.8) (null hypothesis) in the UC group; assuming an alpha level of 0.05 and a two-sided, two-sample *t* test. Assuming 20% dropout, 49 patients are required in the HPA group and 25 patients in the UC group (total sample size 74).

It is expected that up to 50% of MS patients have severe cognitive compromise, and will not be able to complete SEIQoL-DW, in these the only primary endpoint will be the POS-S-MS. We aim to recruit 50 patients in the HPA group and 25 patients in the UC group, thereby achieving an exact 2:1 ratio of intervention to control.

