#### Statistical analyses

Continuous data will be summarized using means, medians, SDs, minimums and maximums. Between-group comparisons will employ either the two-sided unpaired *t* test or Wilcoxon’s two-sided two-sample test for non-normal data. Distributions will be tested for normality using the Shapiro-Wilk test. Correlations will be estimated using Spearman’s or Pearson’s coefficients. Categorical data will be compared by χ2 or Fisher’s exact test.

Longitudinal changes in SEIQoL-DW and POS-S-MS will be analyzed using linear mixed models for longitudinal data [48,49]. All tests will be two-tailed. *P* values <0.05 will be considered significant. For the primary intention-to-treat analyses, multiple imputation of missing values will employ Rubin’s approach. The analyses will be performed with Stata Statistical Software, release 12 (StataCorp LP, College Station, TX, USA), or SAS, release 9.2 (SAS Institute Inc., Cary, NC, USA).

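### Two primary outcomes are each given the full two-sided 0.05 with no rule linking them, so if success on either one counts, the family-wise error is about 9–10% rather than 5%

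*Protocol article*

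**What the plan says.** Four places in the protocol article bear on this.

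- **Primary outcomes** lists two outcomes side by side: "Primary outcomes are changes in patient HRQOL (Schedule for the Evaluation of Individual Quality of Life-Direct Weighting, SEIQoL-DW) and MS symptoms", the latter measured by POS-S-MS. No visit is named there and neither outcome is ranked above the other.
- **Abstract, Methods/design** gives the same two outcomes and attaches two visits. SEIQoL-DW is described as "not assessed in patients with severe cognitive compromise) at three and six months".
- **Sample size** uses one visit only: "for both outcomes we considered changes at three months compared to baseline". Each outcome has its own calculation, and each calculation uses a two-sided alpha of 0.05.
- **Statistical analyses** states "Longitudinal changes in SEIQoL-DW and POS-S-MS will be analyzed using linear mixed models for longitudinal data", then "All tests will be two-tailed", and then the single threshold, P "values <0.05 will be considered significant". It does not say which contrast from the mixed model carries the primary conclusion.

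None of these sections says how the two primary results combine into a conclusion about the intervention.

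**The concern.** Two co-equal primary outcomes, each tested at the full 0.05, give two chances of a false positive. The overall error stays at 5% only if there is a linking rule: both must succeed, they are tested in order, or alpha is shared. The article states none of these, and its sample size section spends the full 0.05 twice.

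This matters because a split result is quite possible. The Sample size section expects that up to half of the patients cannot complete SEIQoL-DW, so the two outcomes are measured in different sets of patients. If one is significant and the other is not, the plan offers no agreed reading, and the natural temptation is to rest the conclusion on whichever succeeded. The choice of visit adds a smaller uncertainty: the trial is sized on three months, but the article never says that three months is the primary visit for analysis.

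**Working it through.** **1. Reproducing the plan's own power.** The inputs are from the Sample size section. I used a two-sided two-sample t test with unequal variances: noncentrality = difference / √(s₁²/n₁ + s₂²/n₂), with Satterthwaite degrees of freedom.

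- SEIQoL-DW, 21 HPA and 11 UC. Difference 31.5 − 12.1 = 19.4. SE = √(12.8²/21 + 19.3²/11) = √(7.80 + 33.86) = 6.45. Noncentrality 3.01, df 14.7, power **80.1%** (stated 80%).
- POS-S-MS, 41 HPA and 21 UC. Difference 0.2 − (−0.4) = 0.6. SE = √(0.5²/41 + 0.8²/21) = √(0.00610 + 0.03048) = 0.191. Noncentrality 3.14, df 28.2, power **85.7%** (stated 85%).

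Both stated powers reproduce at alpha 0.05, which confirms that each outcome was given the full 0.05.

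**2. Error with one test per outcome.** If the tests are independent, the chance of at least one false positive is 1 − 0.95² = **9.75%**. With correlated test statistics, by simulation:

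| Assumed correlation between the two tests | At least one false positive |
|---|---|
| 0 | 9.75% |
| 0.3 | 9.5% |
| 0.5 | 9.1% |
| 0.7 | 8.3% |

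The document gives no correlation, so these are assumptions. Incomplete overlap of the patients favours the upper rows. When one test uses a fraction f of the patients in the other, a patient-level correlation r becomes roughly r√f between the tests. With f = 0.5, a correlation of 0.5 between the tests would need r ≈ 0.5/√0.5 = 0.71.

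These rates count errors in either direction. Errors in favour of HPA are about half: 1 − 0.975² = 4.9% under independence, against a nominal 2.5%. The relative inflation is about the same.

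**3. Error if each outcome were also tested separately at each visit.** Four tests at 0.05 give 1 − 0.95⁴ = 18.5% under full independence. The same patients are seen at both visits, so that is a ceiling. With assumed correlations of 0.5 to 0.8 between visits and 0 to 0.5 between outcomes, simulation gives 14.0% to 17.3%, or about **14–17%**.

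**4. Effect of sharing alpha.** At 0.025 per outcome the error is at most 5% (1 − 0.975² = 4.94% if independent). At the stated numbers, power becomes:

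| Outcome | n (HPA/UC) | Power at 0.05 | Power at 0.025 |
|---|---|---|---|
| POS-S-MS | 41/21 | 85.7% | 77.5% |
| SEIQoL-DW | 21/11 | 80.1% | 69.3% |

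**The case against.** The strongest reply is that this is a condensed article. The primary contrast, the order of testing and the handling of multiplicity are commonly left to a full protocol or analysis plan that is not shown. The threshold sentence is also generic: it covers every test and does not say that any single significant result proves effectiveness. This stands in part. An unseen document may contain a rule, and the condition that either outcome suffices is a reading of the article, not its words. But the article is not silent on alpha. It fixes 0.05 for all tests and allots the full 0.05 to each primary outcome, so a later split of alpha would undercut the power it states.

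A reader might go further and infer four tests, with an error close to 19%. The text does not support that as the main figure. The Primary outcomes section names no visit, and the two visits in the abstract may simply be the assessment schedule. A longitudinal mixed model can yield one test per outcome, and the sample size points to three months. The upper figure also needs results at the two visits to be uncorrelated in the same patients.

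A reader might also infer that both outcomes must succeed, and so that the trial has too little joint power. The protocol states no such requirement. It powers the outcomes separately, and for patients with severe cognitive compromise it makes POS-S-MS the only primary endpoint. Joint power is therefore not a criticism of the plan as written.

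**Conclusion.** The point holds in a limited form. As written, the plan has two co-equal primary outcomes, the full two-sided 0.05 for each, and nothing linking them. If either outcome is enough to claim effectiveness, the two-sided family-wise error is about 9–10%, nearly double the nominal 5%. That figure assumes one test per outcome and a correlation between the tests of 0 to 0.5. The 14–17% range applies only if each visit is also tested separately, under the correlations assumed above.

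This should be put right because it governs how the main result is read. It does not invalidate the design or the data, a document not shown may already deal with it, and it can be settled by wording alone. I would rank it as a recommended correction, not an essential one.

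**What to change.** Before unblinding, state two things.

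1. **Primary contrast.** The three-month between-group difference from the mixed model is primary for each outcome, because that is the change on which the trial is sized. Six-month contrasts are secondary.
2. **Error control across the two outcomes at 5%.** One way is a fixed sequence at two-sided 0.05: POS-S-MS first, then SEIQoL-DW only if POS-S-MS is significant. POS-S-MS is the natural first test because it is assessed in all patients (by the carer version where needed) and drives the sample size. This order is a choice that the documents do not compel.

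The fixed sequence needs no extra patients and leaves POS-S-MS its full 0.05. Its cost is that SEIQoL-DW cannot be claimed as confirmatory if POS-S-MS fails.

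Holm's procedure is an acceptable alternative if the investigators want either outcome to be able to succeed alone. Its worst-case power is that at 0.025: about 77% for POS-S-MS and 69% for SEIQoL-DW at the stated numbers, so the stated power would need restating. Restoring the planned power at 0.025 with 2:1 allocation would take about 50/25 evaluable patients for POS-S-MS and 28/14 for SEIQoL-DW. The first of these equals the whole recruitment target of 75, with no allowance for dropout.

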### Nested qualitative study

The qualitative study consists of two parts: personal, semi-structured interview with MS patients and carers, and focus group meetings (FGMs) of patients’ caring physicians. The aim is to evaluate the experience of participants in order to gain insights into the strengths and weaknesses of the HPA.

#### Informed consent

Prior to participation, potentially eligible qualitative study participants (patients and carers who received the HPA and caring physicians of patients) will be approached by the center PI or a HPA team member, and asked to provide informed consent to participate.

#### Personal semi-structured interviews

We will use a purposive sampling technique to identify consenting HPA dyads in whom primary outcomes (SEIQoL-DW and POS-S-MS) were either among the highest or lowest of the distribution, at the three- or six-month follow-ups. For the dyads thus identified, patients and carers will be interviewed separately, within six months of trial completion. Interviews will be face-to-face, conducted by a trained psychologist in the patient’s home, last for a maximum of 60 minutes (patients) or 90 minutes (caregivers), and will be audio-recorded and transcribed in full. Interviewees will be asked about the acceptability and utility of the HPA intervention as a whole and other issues that arise or seem pertinent (for example relation with professionals, timing, integration with current care). The interviewer will also note participant behavior and other potentially useful non-verbal aspects that emerge. Only carers will be interviewed if the patient has severe cognitive compromise. A minimum of 12 dyads (four at each center) will be included, with sampling continuing until no new themes emerge from the data (data saturation) [50].

#### Focus group meetings

Three FGMs will be conducted (one at each center), their objective is to reveal physicians’ experiences and views about the study intervention. Positive and negative aspects will be solicited. All caring physicians of patients who received the HPA will be invited to participate. Each FGM will be audio-recorded, has a moderator (a trained psychologist) and co-moderator, and an expected minimum of five physician participants.

#### Analysis

The methods of framework analysis [50-52] will be applied to the data. Framework analysis uses a systematic approach to analyzing the content of interviews and FGMs, to thereby identify themes and categories of responses. The interviewers/moderators will review the audio recordings and written notes, and produce interview/meeting transcripts. Interviews and FGMs will be analyzed in successive steps, each corresponding to an increasing level of generalization [53]. Two researchers will analyze the interviews and FGMs, first independently and then jointly. Each FGM report will be submitted to FGM participants for review (respondent validation). The interview and FGM reports will then be considered jointly to produce a more comprehensive analysis of the data (triangulation) [54].

### Study organization

The study investigators/committees are reported in Appendix 1. The trial steering committee is the main decision-making body. It consists of local PIs, patient and consumer representatives, and experts in MS, palliative care, rehabilitation, and methodology. The steering committee meets at least once a year and is the study writing committee (on behalf of all investigators).

The IDSMC is chaired by a palliative physician, and includes a neurologist and methodologist. The IDSMC met (via teleconference) before starting accrual; subsequent teleconferences are scheduled every four months, and at trial termination. IDSMC reports are sent to the trial steering committee.

The qualitative study panel is responsible for planning, conducting and analyzing the qualitative study. It consists of two psychologists with expertise in qualitative research, and the psychologists who will conduct interviews and FGMs.

Trial data are entered into a web-based, password-protected data management system/eCRF that permits edit-audit trails (by authorized trained personnel). Paper copies of eCRFs and any (anonymized) supporting documentation is stored securely at participating centers, with identifying contact details and signed consent forms stored separately, for seven years.

## Discussion

PeNSAMI is a RCT with a nested qualitative study designed to test the effectiveness of a HPA on people with severe MS and their carers. This trial will primarily assess the effect of the HPA on patient HRQOL and symptoms; secondarily it will assess patient functional status and mood; carer HRQOL, mood and caregiving burden; costs, incorporation with standard care, unplanned hospital admissions, referrals to hospice, and deaths over the six-month period.

To our knowledge, this is the first clinical trial of a palliative approach to people with severe MS that adopts a single-blind (examiner) and multicenter design. By also evaluating the experiences of the key players involved in the HPA, we will better identify intervention strengths and limitations. Integration of these qualitative findings with the quantitative findings will maximize possibilities for improving the HPA [55]. Additionally, careful documentation of the content, processes and outcomes of the intervention will make possible its replication and wide implementation [55].

We decided on a randomized controlled study because of its potential to produce unbiased data on intervention efficacy. UC was considered the most suitable comparator, since a sham intervention was not feasible. Note, however, that regular outcome assessment with frequent contacts ensures that the control group receives a considerable amount of attention. For ethical reasons and to encourage participation, we decided to assign eligible dyads to HPA vs. UC in a 2:1 ratio, and also to offer control dyads the HPA at the end of follow-up.

### Expected benefits

Fragmentation of care across different health care sectors is a recognized problem, particularly for patients with complex care needs and co-morbidities. The HPA is not intended to replace existing services but to complement, collaborate with, and enhance them, minimizing duplication of effort. The potential for HPA integration into existing services is a strength of our trial.

Health professionals caring for people with severe MS themselves have several unmet needs and feel overstretched in their daily work. Physicians express feelings of helplessness or anger in the face of cuts in funding, and having to work under time pressure and in complex social situations [11]. They also feel hampered by inadequate communication skills (not taught at university) [10,56].

In addition to providing valuable data, the trial affords interdisciplinary training for the health professionals involved. By making palliative care professionals work with MS neurology and rehabilitation professionals [57], the trial should encourage greater awareness and more effective management of people with severe MS.

Effective exchange between the dyad, the caring physician and the HPA team should result in treatment decisions in the best interests of MS patients and the avoidance of inappropriate hospital admissions. It is also expected that the trial will empower people with severe MS (and their carers) by providing them with information and education on their condition, encouraging them to be active participants in care and decision making, including advance health directives where appropriate.

### Limitations and concerns

We estimated a sample size of 75 patients, which is rather small for a phase II/III trial. We based our sample size estimate on published data: for POS-S-MS, these data come from MS patients with similar characteristics to our study population [8], and for SEIQoL-DW, from people with severe MS or other neurodegenerative conditions [15]. In view of our limited sample size, we used adaptive (minimization) randomization to ensure comparability of study arms.

Another limitation is that, in contrast with previous trials [8,15], our trial did not originate from palliative services, which in theory can directly address needs identified. Our HPA aims to activate existing services or bring them to the attention of the dyad. The extent to which these aims are achieved cannot be predicted.

Finally, having a blind examiner renders trial procedures considerably more complex: the blind examiner must have no contact with the HPA team; dyads must be briefed about the importance of keeping the examiner blinded; and, prior to three- and six-month visits, the blind examiner is instructed to caution dyads against disclosing their assignment or mentioning issues related to study procedures. In addition, costs and intensity of care outcomes, as assessed by the MSCQ, are assessed by telephone interviews at three and six months conducted by an independent professional - again to prevent examiner unmasking.

## Abbreviations

Core-POS: Core-Palliative care Outcome Scale
eCRF: electronic case record form
EDSS: Expanded Disability Status Scale
EQ-5D: European Quality of Life Five Dimensions
FGM: focus group meeting
FIM: Functional Independence Measure
GP: general practitioner
HADS: Hospital Anxiety and Depression Scale
HPA: home-based palliative approach
HRQOL: health-related quality of life
IDSMC: Independent Data and Safety Monitoring Committee
MSCQ: Multiple Sclerosis foundation Costs Questionnaire
MS: multiple sclerosis
PI: principal investigator
POS-S-MS: Palliative care Outcome Scale-Symptoms-Multiple Sclerosis
RCT: randomized controlled trial
SAE: serious adverse event
SD: standard deviation
SF-36: Short Form 36
SEIQoL-DW: Schedule for the Evaluation of Individual Quality of Life - Direct Weighting
UC: usual care
ZBI: Zarit Burden Interview
